## Discussion

Internet based self-help for PD has proven to be effective. However, existing interventions focus on treating a full-blown disorder, while sub-clinical PD is highly prevalent and can develop into full-blown PD. This study is a randomised controlled trial aimed to evaluate an Internet based self-help intervention for sub-clinical and mild PD compared to a waiting list control group. The primary outcome measure is the severity of panic and anxiety symptoms. Secondary outcome measures include depression, quality of life, loss of production and health care consumption.

### Methodological considerations

The primary research question is whether DPO is an effective intervention for mild and sub-clinical PD. We hypothesise the experimental group will show more improvement on the outcome measures than the control group, because the experimental group receives an accessible intervention tailored for its specific mental health problems.

A limitation of this study is the low number of exclusion criteria. The presence of a comorbid disorder or substance abuse is not an exclusion criterion. Comorbidity may influence this study's outcome measures, because panic symptoms may not be the participant's primary mental health problem. However, in reality, many people who suffer from panic symptoms have comorbid mental health problems, especially other anxiety disorders and depression [6]. Therefore, it is preferable not to exclude participants based on DSM diagnoses for these disorders. An indication of the effects of comorbidity on the effectiveness of DPO could be obtained by mediator analyses.

Both a strength and a limitation of this study is that, apart from the diagnostic interview, the measurements are conducted online. Some evidence suggests psychometric properties may change when a test is conducted via the web [36,37]. Consequently, results of this study may differ from studies into panic interventions that applied paper-pencil questionnaires. On the other hand, the strength of online self-report measurements is the accessibility of participation [38]. Therefore, this study is feasible and should be able to answer the research questions.

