### Randomisation and procedure

After screening and completion of the baseline questionnaires (t0), the participant will be contacted for a diagnostic interview by telephone. The interview will be conducted within two weeks after baseline by a trained and experienced interviewer. All participants will be randomised to one of the two groups, regardless of the presence or absence of a diagnosis. Randomisation will be stratified for the presence or absence of agoraphobia symptoms (PDSS-SR item 4 score > 1) and the use of medication. Randomisation lists are generated with a computer program. Blinding of the participants and researchers is not possible due to the design of this research. The post-treatment assessment (t1) is scheduled at 3 months after baseline. Both the baseline and the post-treatment assessments are self-report and will be conducted through the Internet.

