### Instruments

All variables will be measured at t0 and t1, except for demographic data, the diagnosis and satisfaction with the intervention. Demographic data and diagnosis are only measured at t0, while satisfaction with the intervention will only be measured at t1.

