#### Diagnosis

The Composite International Diagnostic Interview (CIDI) [22] will be used to ascertain the presence or absence of PD, other anxiety disorders and depression. The CIDI has been developed by the WHO and is an extensive, fully structured diagnostic interview to assess DSM-IV Axis-I diagnoses [22]. Only the subscales depression, PD, agoraphobia, GAD, social phobia and post-traumatic stress disorder will be used in this study. The reliability of these subscales is sufficient (inter-rater κ = .94 - .99; test-retest κ = .62 - .84) [23]. In this study, a trained interviewer will administer the CIDI by telephone.

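### Comorbidity is proposed for mediator analyses, but a diagnosis recorded only at t0 can only be examined as a moderator

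*Protocol article*

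**What the plan says.** Under Methodological considerations, the protocol article calls its small number of exclusion criteria a limitation: "Comorbidity may influence this study's outcome measures, because panic symptoms may not be the participant's primary mental health problem". It then suggests an analysis: "An indication of the effects of comorbidity on the effectiveness of DPO could be obtained by mediator analyses".

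Comorbid diagnoses come from the CIDI, which "will be used to ascertain the presence or absence of PD, other anxiety disorders and depression" (Diagnosis). Their timing is fixed under Instruments: "Demographic data and diagnosis are only measured at t0". Under Randomisation and procedure, "The interview will be conducted within two weeks after baseline by a trained and experienced interviewer", and the next sentence reads: "All participants will be randomised to one of the two groups, regardless of the presence or absence of a diagnosis". The other measures, including the CES-D and the BAI, are taken at t0 and t1 with no assessment in between. The Analyses section names neither a mediator nor a moderator analysis.

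**The concern.** The question and the method named for it do not match. The question is whether the treatment effect differs between participants with and without comorbid disorders, which is effect modification. Mediation analysis asks something else: through which intermediate variable, itself changed by treatment, does the treatment act on the outcome? A diagnosis recorded once, at t0, cannot show a change caused by treatment.

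Taken literally, the suggestion would produce an indirect effect close to zero whatever the truth. Someone could then report that comorbidity makes no difference, when the analysis had not examined that question. The data for the right analysis are already being collected.

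**Working it through.** **Inputs.** From Sample size: d = 0.50, two-sided alpha 0.05, power 80%, 64 per group, N = 128. Comorbidity prevalence p and the size of any effect modification are not given. I assume p = 0.3 to 0.7 and, for illustration, a modification of 0.5 SD.

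**1. The plan's own figure.** The normal approximation gives 63 per group. The exact two-sided t-test gives 63.77, rounded up to 64, with power 80.1% at 64 per group. The stated sample size reproduces.

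**2. Mediation through a baseline diagnosis.** The indirect effect is a × b, where a is the effect of allocation on the diagnosis and b the association of the diagnosis with outcome given allocation. Here a = P(diagnosis | course) − P(diagnosis | waiting list), which is 0 in expectation when the diagnosis precedes randomisation. So a × b is 0 in expectation for any b and any interaction.

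**3. Simulation.** 3000 trials of N = 128, p = 0.5, residual SD 1, with a treatment effect of −0.75 SD without comorbidity and −0.75 + 0.50 = −0.25 SD with it (true interaction 0.50):

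| Analysis | Mean estimate (SD) | Significant at 5% |
|---|---|---|
| Indirect effect, a × b | 0.0005 | 2.6% |
| Treatment-by-comorbidity interaction | 0.497 | 28.8% |

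The mediation analysis carries no information on the question. The interaction model estimates the right quantity, but imprecisely.

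**4. What the interaction can detect.** In SD units, with 1:1 allocation within each subgroup and no missing data:

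SE = √[2/(64p) + 2/(64(1 − p))]

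- p = 0.5: SE = √(0.0625 + 0.0625) = 0.354. This is twice the main-effect SE of √(2/64) = 0.177.
- p = 0.3 or 0.7: SE = √(0.1042 + 0.0446) = 0.386.

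The smallest difference detectable with 80% power is (1.960 + 0.842) × SE:

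| p | Detectable difference (SD) | Power for 0.5 SD | Total N for 0.5 SD |
|---|---|---|---|
| 0.5 | 0.99 | 29% | 503 |
| 0.4 or 0.6 | 1.01 | 28% | 524 |
| 0.3 or 0.7 | 1.08 | 25% | 599 |

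The detectable difference between subgroups is thus about twice the main effect for which the trial is sized.

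**The case against.** The strongest reply is that this is a slip of one word in a conditional remark. The sentence says what could be done, it stands in the Discussion, and the Analyses section commits to nothing of the kind. It also states the intended question, so many readers would take *moderator* to be meant. This stands, and it limits the weight of the point. It does not remove it, because the two terms name different models with different results.

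A second reply is that not all comorbidity is measured only at t0. Depressive symptoms (CES-D) and general anxiety (BAI) are repeated at t1. That is true, but the t1 scores are taken together with the outcome, and the BAI is itself a primary measure. Mediation through them would ask whether the course works by way of depression or general anxiety, not whether comorbidity alters its effect.

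A third is that the article does not state outright that the interview precedes randomisation. That order is inferred from the sequence of the text. Even if it were wrong, the diagnosis is a t0 measurement and is never repeated, so it could not serve to trace a change over the course of treatment.

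A reader might go further and infer that the trial's main limitation rests on this analysis as its only safeguard. The article does not support that. It speaks of a limitation, not the main one. It defends broad entry on the ground that comorbidity is common among people with panic symptoms, and it offers the analysis only as a possible indication. Randomisation balances comorbidity in expectation, so the main comparison needs no such safeguard.

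**Conclusion.** The point holds as a minor correction. The article names the wrong type of analysis for the question it raises. For CIDI diagnoses recorded at t0, the indirect effect is zero in expectation whatever the true effect modification. The correct analysis is feasible with the planned data but weak: about 1.0 SD is detectable with 80% power, and power for a difference of 0.5 SD is 25-29%.

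These figures assume a comorbidity prevalence of 30-70%, complete data and no gain from covariate adjustment; loss to follow-up would worsen them and baseline adjustment would improve them. That the interview precedes randomisation is a likely reading, not a stated fact. No primary or secondary result and no sample-size figure depends on the sentence.

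**What to change.** In Methodological considerations, replace the mediator analysis with an exploratory moderator analysis: a treatment-by-comorbidity interaction in the outcome model, with comorbidity defined as any CIDI diagnosis other than PD at t0 (yes/no). Report the interaction as an estimate with 95% CI and do not read a non-significant result as absence of modification.

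Add two statements:

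- With N = 128, only a difference in effect of about 1.0 SD is detectable with 80% power (0.99 to 1.08 SD over an assumed prevalence of 30-70%).
- Substance abuse, which the same paragraph names beside comorbid disorders, is not covered by the CIDI sections used (depression, PD, agoraphobia, GAD, social phobia, post-traumatic stress disorder), so the yes/no variable will not capture it.

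The cost is a change of wording and one additional model. No new data, no change to the sample size and no change to the primary analysis are needed.

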## Conclusion

Existing online interventions for panic symptoms focus on treating full-blown PD, while sub-clinical PD is highly prevalent and may develop into a full-blown disorder. This study evaluates an Internet based self-help intervention for sub-clinical and mild PD. Results will contribute to the ongoing research into Internet based interventions and treatment of panic symptoms.
